## 5.2 Serious and Unexpected Adverse Events

A serious adverse event is defined as: (i) fatal, (ii) life threatening, (iii) requires acute medical treatment, (iv) permanently disabling, (iv) required hospitalisation for treatment, (v) prolongs a hospital stay, (vi) causes malignancy, (vii) causes a congenital abnormality. An unexpected adverse event is defined as an adverse event, the nature or severity of which is not consistent with the applicable product information (Package Insert or Summary of Product Characteristics).

All SAEs will be reported immediately or not later than 24 hours by telephone, facsimile, or email to ([name] or delegated person) at WHO/TDR. The telephone report should be followed by a written report that should fully document the event. Additional laboratory information and clinical data should be supplied as soon as possible, not exceeding 5 days following the event. In case of death, if an autopsy is performed, a copy of the pathological report should be sent to the Sponsor. When the SAE has resolved, a detailed report will be submitted to TDR with a copy kept in the investigator's file.

#

# 6.0 DATA MANAGEMENT

## 6.1 Case Record Form (CRF)

Patient information will be collected in the study Case Record Form (Appendix 1). The CRF must be completed legibly for each patient enrolled in the study, in black ink and signed by the Principal Investigator or authorised trial personnel. Patient records will be kept such that the identity of the patient will not be disclosed, and will be available for inspection by the clinical monitor and the Study Director. For identification purposes, there will be three or four unique identifiers on each form and specimen: initials (name, father's name, grandfather’s name; there are no surnames in Ethiopia), randomisation number, clinic number, and date of sample.

## 6.2 Data management and quality assurance

Sputum specimens will be subject to blind rereading. A SOP for the laboratory will be completed before the trial is initiated. Laboratory equipment will be calibrated according to the manufactures' recommendations (and outlined in the SOP). TDR/WHO as the sponsoring agency will perform monitoring visits and subject data recorded in the CRFs to source data verification.

## 6.4 Data analysis

The database file generated thus will be converted into statistical package STATA software version 7 (STATA Corporation, Texas, USA) and analysed by the study statistician, and PI in collaboration with the study director. Analysis will be both (a) by intention-to-treat, and (b) per protocol (excluding those who did not receive adequate chemotherapy or were withdrawn from the study), including survival analysis.Subjects will be compared based on their assigned treatment using chi-square, Student's t-test or the Wilcoxon rank sum test as appropriate depending on the scale of measurement and the validity of underlying assumptions for the baseline characteristics. Primary and secondary outcomes for each study subject will be recorded as positive (desirable) and negative (not desirable) at a pre-specified time. For primary outcome Chi-square will be used to compare proportions of culture positive and culture negative subjects at the end of the study in the two treatment groups. The effects of confounding variables (such as age and sex) will be adjusted using multiple logistic regression. In model construction, backward elimination will be employed using important independent variables initially. An alpha of 0.10 will set the significance level for entering a variable into the model. Chi-square will also be used to compare differences in each of the three secondary end points. In the whole analysis, an alpha of 0.05 will set the significance level for testing the null hypothesis. In presenting results exact p-value as obtained from the computer program will be presented.

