### ***Primary Outcome measures***

- cure rates at end of treatment (6 months). A cure is defined as one negative sputum culture in patients who did not fail treatment. A treatment failure is defined as:

1. a patient who is persistently smear positive by five months of treatment
2. a patient who becomes smear negative but positive again at or after five months of treatment (note: sputum positivity before this time is not considered a treatment failure)

- ***Secondary outcome measures***
- early response rates: proportion of patients with negative culture results at 8 weeks after initiation of therapy
- proportion of patients with relapses during the 72 weeks follow up period after the end of treatment. A relapse is a patient previously treated for tuberculosis who has met the case definition of cure (as defined above) and been declared cured by a physician and who has now been diagnosed with bacteriologically positive (two positive smears and culture positive) tuberculosis. If there is discordance between smear and culture results, a clinical decision will be made regarding further management: (i) smear positive, culture negative, and (ii) smear negative and culture positive.
- cure rates in HIV positive TB patients
- proportion of patients with clinical deterioration of pulmonary tuberculosis with the need for hospitalisation
- proportion of patients with *serious* adverse events any time during chemotherapy
- proportion of patients with any adverse events during chemotherapy
- proportion of patients completing treatment (defined as patients who achieved a total of 54 out of 56 doses in the first eight weeks of treatment AND 107 out of 112 doses at a daily rate during the subsequent 16 weeks of treatment) within each group. (96% doses taken considered as completed in intensive and maintenance phases).
- Proportion of patients who developed MDR-TB

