***Study withdrawals***

- AFB smear positive patients found later to be culture negative. These patients will be withdrawn from the study but they will be assessed clinically to see if treatment should be continued or not. (This occurs in 1-5 % of newly diagnosed cases).
- Patients withdrawing consent in the course of the trial
- Antiretroviral therapy initiation within the first six months of anti-TB medication.
- AFB smear positive patients at week 20 whose sputum culture and DST confirm resistant to isoniazid and rifampicin (MDR TB)
- Drug toxicity necessitating interruption of treatment

Patients who withdraw from study or are lost to follow up will however still be included in the intention to treat (ITT) analyses set.

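### The per-protocol rule removes confirmed-MDR treatment failures at week 20, so that analysis can hide an FDC deficit and cannot serve as a check on ITT

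*Protocol*

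**What the plan says.** The rule comes from combining four places in the protocol.

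- **Failure (section 2.2, primary outcome).** One of the two definitions of treatment failure is "a patient who is persistently smear positive by five months of treatment". The other is a return to smear positivity at or after five months. Cure requires a negative culture in a patient who has not failed.
- **Withdrawal (section 3.2, Study withdrawals).** One of the five reasons is "AFB smear positive patients at week 20 whose sputum culture and DST confirm resistant to isoniazid and rifampicin (MDR TB". Others are "Drug toxicity necessitating interruption of treatment", the start of antiretroviral therapy (ART) in the first six months, and "AFB smear positive patients found later to be culture negative". The flow chart for MDR TB repeats the exclusion of week-20 MDR cases.
- **Timing (section 3.6).** The notes to the schedule treat the week-20 smear as the five-month smear. Sensitivity testing of the stored week-0 sample is done only if week 20 is positive.
- **Analysis sets.** Section 6.4 names an ITT analysis and one "per protocol (excluding those who did not receive adequate chemotherapy or were withdrawn from the study", and ranks neither above the other. Section 3.2 adds: "Patients who withdraw from study or are lost to follow up will however still be included in the intention to treat (ITT) analyses set".

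**The concern.** A patient who is smear positive at week 20 with confirmed MDR has failed treatment by the trial's own definition, yet leaves the per-protocol denominator as a withdrawal. The exclusion depends on the outcome.

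It cannot be defended as a late eligibility check. Baseline sensitivity is tested only in patients who are positive at week 20, so baseline resistance in a patient who is smear negative at week 20 is never looked for and never leads to exclusion.

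Section 4 states an equivalence objective with a 4-point margin. Analysts look to per-protocol in such a trial because ITT can blur a real difference. A per-protocol set that drops failures loses that function: agreement with ITT may be produced by the rule, and disagreement is hard to interpret. The subject also matters. Section 2.1 gives prevention of drug resistance as a main reason for FDCs, and section 2.2 lists development of MDR-TB as a secondary outcome.

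**Working it through.** **1. The plan's own figure.** Section 4 gives control cure 96%, margin 4 points, one-sided 5%, power 90%, 10% dropout and 498 per arm. The Farrington-Manning score test, with constrained null rates 0.972 and 0.932, gives a null variance of 0.972×0.028 + 0.932×0.068 = 0.0906. Then

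n = (1.645×√0.0906 + 1.282×√(2×0.96×0.04))² / 0.04² ≈ 452.

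Dropout gives 452×1.1 = 497 or 452/0.9 = 502. The stated 498 is reproduced closely, so nothing below rests on a wrong sample size. Evaluable patients per arm: 498×0.9 = 448.

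**2. Effect of the rule on the per-protocol contrast.** Let m be the proportion of an arm withdrawn as week-20 MDR failures. If true cure is p, per-protocol cure is p/(1−m) on 448(1−m) patients. I take a true deficit equal to the margin (96% v 92%), where the false acceptance rate should be 5%. The test is the one-sided one of section 4, on which the trial is sized. The documents give no value for m, so I vary it.

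Worked case, m = 1% in the FDC arm and 0 in control:

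- FDC per-protocol cure = 0.92/0.99 = 0.9293 on 443.5 patients
- difference = 0.96 − 0.9293 = 0.0307
- SE = √(0.9293×0.0707/443.5 + 0.96×0.04/448) = 0.0153
- chance of acceptance = Φ((0.04 − 0.0307)/0.0153 − 1.645) = Φ(−1.04) ≈ 15% (16% by simulation)

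Simulated results (Wald):

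| MDR failures, FDC / control | FDC patients dropped (of 448) | Per-protocol cure, FDC v control | Difference (points) | False acceptance, per-protocol alone |
|---|---|---|---|---|
| 0 / 0 | 0 | 92.0% v 96.0% | 4.0 | about 5% |
| 0.25% / 0 | 1.1 | 92.2% v 96.0% | 3.8 | 7% |
| 0.5% / 0 | 2.2 | 92.5% v 96.0% | 3.5 | about 10% |
| 1% / 0 | 4.5 | 92.9% v 96.0% | 3.1 | 16% |
| 2% / 0 | 9.0 | 93.9% v 96.0% | 2.1 | 37% |
| 4% / 0 | 17.9 | 95.8% v 96.0% | 0.2 | 88% |
| 1% / 0.5% | 4.5 | 92.9% v 96.5% | 3.6 | about 10% |
| 1% / 1% | 4.5 | 92.9% v 97.0% | 4.0 | about 5% |

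The last row marks the limit of the point: the error rate rises when MDR failures are more frequent on FDCs, not when they are equally frequent.

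**3. ITT in the same scenarios.** With the MDR failures kept and counted as not cured, the contrast stays at 4.0 points and false acceptance stays near 5%. Requiring both analyses to succeed also gives about 5% or less.

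**4. Baseline culture-negative patients.** Section 3.2 says of them "This occurs in 1-5 % of newly diagnosed cases", so 498×1% to 498×5% is about 5 to 25 per arm. Kept in ITT and balanced between arms, they shrink a 4.0-point difference to 4.0×0.99 = 3.96 or 4.0×0.95 = 3.80. False acceptance becomes 5.3% to 6.6%, depending on their share and on how they are scored. If they were all scored not cured, power at equal 96% cure with 498 per arm would fall from 94% to 90% (at 1%) or 72% (at 5%).

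**The case against.** **ITT already counts these patients.** This stands and limits the harm. The inflated rates need per-protocol to decide alone, and in the worst case the two sets would visibly part (4.0 v 0.2 points). But section 6.4 does not rank the analyses, and a second analysis that deletes failures adds no reassurance to the first.

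**MDR failures should be few.** Patients are previously untreated and treatment is observed, so 4% in one arm and none in the other is an extreme. This also stands, and the lower rows of the range deserve more weight. Still, expected non-cure is only 4%, and removing about four or five FDC failures roughly triples the error rate.

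**Stronger readings that the protocol does not support:**

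- A reader might infer that all week-20 failures leave the per-protocol set. Only those with confirmed MDR are on the withdrawal list as such.
- A reader might class toxicity and ART withdrawals as failures too. Section 2.2 defines failure by smear at or after five months, so they are not. Leaving incompletely treated patients out is the ordinary meaning of per-protocol. The exclusion is still post-randomisation and possibly informative, toxicity most plausibly so.
- A reader might conclude that ITT is biased as well, because Day-0 culture-negative patients stay in it. That culture precedes treatment, so randomisation balances them; the effect is dilution of at most about 0.2 points. The protocol does not say that they count as not cured. Scoring of withdrawn patients is a detail that the analytical plan of section 6.5 may settle. Per-protocol, which drops them as withdrawals, already gives a result without them.

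**Conclusion.** Wrong as written, for one specific rule. Sections 2.2, 3.2 and 6.4 together remove protocol-defined primary-endpoint failures from the per-protocol set on the basis of a post-randomisation outcome. An analytical plan that follows the protocol would inherit this, so it is not a detail left for later.

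The size depends on an MDR rate that the documents do not give. At a true 4-point deficit, with MDR failures in the FDC arm only, false acceptance on per-protocol alone goes from about 5% to between 7% and 37% for MDR rates of 0.25% to 2%. The 88% at 4% is an outer bound, not an expectation. With equal MDR rates in both arms there is no inflation. ITT is sound on this point, and the toxicity, ART and culture-negative withdrawals do not carry the same fault.

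**What to change.** Add to section 6.4: any patient who meets the section 2.2 definition of treatment failure, including a week-20 smear-positive patient with confirmed MDR who is referred out of the study, counts as not cured in both ITT and per-protocol, and the per-protocol exclusion for withdrawal does not apply to that patient. The clinical referral and withdrawal rules in section 3.2 and the flow chart need no change, and no new data are required.

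Optional: a sensitivity analysis that leaves out Day-0 culture-negative patients in both arms, to show the small dilution and any loss of power.

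Cost: a sentence or two of wording. The per-protocol cure rate will look slightly less favourable.

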# 4. STATISTICAL CONSIDERATIONS

The objective of the study is to demonstrate that FDCs have equivalent efficacy to the loose formulations.

Sample sizes of 498 from the intervention group and 498 from the standard group achieve 90%

power at a 5% significance level using a one-sided equivalence test of proportions when the

proportion of patients cured in the comparator group (Ps) is 96% and the maximum allowable difference (clinically acceptable difference) between proportions in the two treatment groups that still results in equivalence (the range of equivalence) is 4%. A sample size of 498 in each group is estimated with dropout rates of 10%. Two study sites will conduct the trial and contribute to the total sample size. Ethiopia will contribute a total of 498 subjects (249 in each arm) per country to reach the sample size of 996.

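### The primary outcome is assigned a chi-square test of no difference, which cannot show the equivalence within 4 points that the trial was sized for

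*Protocol*

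**What the plan says.** Section 4 of the protocol gives the aim: "The objective of the study is to demonstrate that FDCs have equivalent efficacy to the loose formulations". It claims 90% "power at a 5% significance level using a one-sided equivalence test of proportions when the" comparator cure rate is 96%. The largest difference "that still results in equivalence (the range of equivalence) is 4" percentage points. On the numbers: "A sample size of 498 in each group is estimated with dropout rates of 10"%.

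Section 6.4 fixes the analysis: "For primary outcome Chi-square will be used to compare proportions of culture positive and culture negative subjects" in the two arms. For the whole analysis, "an alpha of 0.05 will set the significance level for testing the null hypothesis". Results are to be reported as exact p-values. Logistic regression is added to adjust for confounders. Analyses by intention to treat (ITT) and per protocol are both planned, and neither is named as primary.

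The 4-point margin appears only in section 4. Section 6.4 has no margin-based hypothesis and no interval for the difference. Section 6.5 says that an analytical plan will be finalised before analysis begins.

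**The concern.** The two sections describe different tests. A margin test has as its null that FDC is worse by 4 points or more, and rejecting it supports the trial's claim. A chi-square comparison of two proportions has as its null that the arms are equal, and rejecting it says only that they differ. Failing to reject shows neither equality nor closeness within 4 points, and it becomes more likely as the data become less precise.

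The level does not match either: one-sided 5% in section 4, but 0.05 for an ordinary chi-square, which is in effect two-sided, in section 6.4.

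At stake is whether the named primary analysis can support the stated objective at all. The only chi-square result that anyone could offer in support of equivalence is a non-significant one, and its error rate is not the 5% behind the sample size.

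**Working it through.** **Inputs from section 4.** Comparator cure 96%; margin 4 points; one-sided alpha 5%; power 90%; 498 per arm; dropout 10%, so 498 × 0.9 = about 448 evaluable per arm. Assumed, because not stated: a true difference of zero for the sizing.

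**1. The planned size is that of a margin test.** The Farrington-Manning score formula uses null rates of 0.932 and 0.972, which are 4 points apart.

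- Null SD term: √(0.932·0.068 + 0.972·0.028) = 0.3009
- Alternative SD term: √(2·0.96·0.04) = 0.2771
- n = [(1.645·0.3009 + 1.282·0.2771)/0.04]² = 452 per arm
- 452 × 1.10 = 497.2, rounded up to 498, the protocol's figure (dividing by 0.9 instead gives 503)

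A two-sided equality test of 96% v 92% needs [(1.960·√(2·0.94·0.06) + 1.282·√(0.96·0.04 + 0.92·0.08))/0.04]² = 739 per arm, or 822 with dropout. So section 4 was not built on the test named in section 6.4.

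**2. Neither chi-square result settles the question.** The difference is FDC minus loose, the chi-square is uncorrected, and the Wald lower 90% limit is difference − 1.645·SE.

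| FDC | Loose | Difference | SE | Chi-square p | Lower 90% limit | Margin met? |
|---|---|---|---|---|---|---|
| 417/448 (93.1%) | 430/448 (96.0%) | -2.9 points | 1.52 | 0.056 | -5.4 | No |
| 483/498 (97.0%) | 493/498 (99.0%) | -2.0 points | 0.89 | 0.024 | -3.5 | Yes |

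Score limits are -5.5 and about -3.65, with the same conclusions.

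**3. Error rate if non-significance were read as equivalence.** Take true rates of 92% v 96%, exactly at the margin.

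- 448 per arm: pooled SE √(2·0.94·0.06/448) = 0.01587; SE under the alternative √((0.96·0.04 + 0.92·0.08)/448) = 0.01581. P(non-significant) = Φ((1.96·0.01587 − 0.04)/0.01581) = 0.287. Simulation of 400,000 trials gives 0.28.
- 498 per arm: 0.242 by the same formula; simulation 0.24.
- A margin test at the same rates passes in about 5% (simulation).

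**4. Power once the margin is used.** With 96% in both arms and 448 evaluable per arm, the one-sided 5% margin test has about 90% power (score) or 92% (Wald). The sample size need not change for one analysis at 96% cure.

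**5. Power if both sets must succeed.** The protocol keeps withdrawn and lost patients in the ITT set but does not say how they are scored. If the 10% who drop out are counted as not cured (an assumption), the ITT cure rate is 0.96 × 0.9 = 86.4%. With 498 per arm the SE is √(2·0.864·0.136/498) = 0.0217, and the ITT power is Φ(0.04/0.0217 − 1.645) = about 58%. Simulation of success in both sets gives about 56%. If dropouts were left out of the analysis, the power would stay at the 90% to 92% of step 4.

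**The case against.** **The later analytical plan could supply the margin test.** It could, and the absence of a confidence interval or success rule from a protocol would not by itself be a finding. But section 6.4 is not silent. It names a specific primary test that does not fit section 4, and section 6.5 withdraws nothing. A later margin analysis would depart from the protocol's named test.

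**A reader might infer that the plan treats a non-significant result as success.** The protocol does not say so. It gives a test, a level and a reporting format, but no decision rule. The 28% and 24% are therefore conditional figures and do not measure what the trial team would do. This part of the objection stands in full.

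**A reader might quote a much larger error at lower cure rates.** At 82.4% v 86.4% with 498 per arm, the chi-square is non-significant in about 59% of simulated trials. But 86.4% is not in the protocol. It arises only if all dropouts are scored as not cured, so the 59% cannot carry the point.

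**A reader might argue that two-sided equivalence is impossible because 96% plus 4 points reaches 100%.** That confuses the true rate with the interval. With 448 per arm, the 90% interval for the difference has a half-width of 1.645·√(2·0.96·0.04/448) = 2.2 points, so an upper limit of +4 can be tested. The reason to call the design non-inferiority is that section 4 specifies a one-sided test.

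**Logistic regression is also planned.** It is there to adjust for confounders. It yields an odds ratio, for which no margin is given, so it does not fill the gap.

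**Conclusion.** The mismatch is real and must be fixed. Section 4 sets an equivalence objective and a size that reproduces as a one-sided margin test; section 6.4 assigns the primary outcome a test of equality. The two worked results show that the chi-square and the margin can disagree in either direction. This conclusion needs no assumption about how the team would interpret a p-value.

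The size of the possible error does need one. If p>0.05 were taken as equivalence, an FDC truly 4 points worse would pass in about 28% of trials with 448 evaluable per arm, or 24% with 498, instead of about 5%. The sample size itself is not in question here: 498 per arm agrees with the margin test.

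**What to change.** In section 6.4, replace the primary-outcome chi-square sentence with wording such as:

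> The primary analysis estimates the difference in cure proportion (FDC minus loose) with a two-sided 90% confidence interval (one-sided 5%, score method). FDC is concluded to be non-inferior if the lower limit is above -4 percentage points.

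Then:

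- Describe the one-sided test in section 4 as non-inferiority, and align the level in section 6.4 with it.
- Keep chi-square for descriptive comparison only.
- Apply the same interval to the ITT and per-protocol sets already planned, state which is primary, and say how dropouts are scored in the ITT set.
- If success in both sets is to be required, restate the power first. It is about 56% if dropouts count as not cured.

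The cost is wording in sections 4 and 6.4 and in the analytical plan, with no new data or patients for a single primary set at 96% cure. A rule requiring both sets, or an ITT set with dropouts scored as not cured as the primary one, may not be free in this way.

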## 3.5 Treatment Allocation

Patients are to be allocated to the different treatment arms according to a computer generated randomisation list. The randomisation list will be prepared and kept by the Study Director. Each centre will be provided with a batch of sealed envelopes. The total number of allocated envelopes will correspond to their expected intake to the study. Therefore, each patient will be allocated randomly **either** the FDCs regimen **or** the separate drug regimen. Each sealed envelope will contain a sequential patient code (randomisation number) and a Treatment Card printed with the details of one of the two regimens to which the patient will be allocated. Only a specially assigned person will open the envelope and dispense the drugs to the patient. No other study personnel will be present at the time of drug allocation. This information will, therefore, only be known to the assigned dispenser and the patient. Randomisation is considered to have taken place once the envelope containing the code for the drug regimen is opened. Once a patient is allocated a randomisation number must not be used for other patients, in the event that the patient decides to withdraw voluntary consent before study drug administration. A treatment allocation log will be kept by the specially assigned person and will not be available to the investigators until the analysis has been concluded, or unless the patient’s physician requires this information for safety reasons.

The PI and the clinicians will remain blinded to the drug regimens of individual patients throughout the study.

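### The primary cure comparison has no country term although balanced arms are planned within each country: a small, conservative loss of precision that costs nothing to remove

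*Protocol*

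**What the plan says.** **Allocation.** Protocol section 3.5 describes a computer-generated randomisation list held by the Study Director. On distribution it says: "Each centre will be provided with a batch of sealed envelopes". The number of envelopes follows each centre's expected intake. The section mentions neither stratification nor blocking.

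**Country split.** Section 4 says: "Ethiopia will contribute a total of 498 subjects (249 in each arm) per country", to reach 996 in all. Only Ethiopia is named. With two sites and 996 patients, the other country also supplies 996 − 498 = 498, or 249 per arm. This is a recruitment plan inside the sample-size paragraph.

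**Primary analysis.** Section 6.4 says: "For primary outcome Chi-square will be used to compare proportions of culture positive and culture negative subjects". No country or centre term is attached. The section goes on to a multiple logistic regression for confounders, with age and sex as its examples and backward elimination to choose variables. It reports exact p-values and names no confidence interval. Both intention-to-treat and per-protocol analyses are planned.

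**Later plan.** Section 6.5 leaves the analytical plan to be finalised before the analysis begins.

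**The concern.** Recruitment and envelope supply are organised by place, but the primary test ignores place. The protocol gives some reason to expect the countries to differ:

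- HIV-positive patients enter at different CD4 thresholds in Nigeria and Ethiopia (section 3.2).
- Continuation-phase dosing follows each country's own DOTS practice (section 3.6).
- CD4 thresholds for referral to antiretroviral care differ by country (section 3.9), and starting such treatment in the first six months is a ground for withdrawal. Per-protocol losses could therefore differ by country too.

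When a prognostic factor is balanced across arms, leaving it out of the analysis does not bias the difference, but it does overstate the standard error. The trial aims to rule out a loss of 4 points, so needless width costs some power. A single pooled 2×2 table also does not show whether the two countries agree.

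**Working it through.** **Inputs.** From section 4: 498 per arm, 249 per arm per country, 96% cure (taken as equal in both arms), 4-point margin, one-sided 5%, 90% power, 10% dropout. Assumed, because the protocol does not give it: the gap *d* in cure rate between countries. At a 96% mean, *d* can run from 0 to 8 points (8 points means 100% v 92%).

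**1. The plan's own figure.** The Farrington-Manning formula uses null rates constrained to differ by 4 points (0.972 and 0.932):

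- null variance 0.972×0.028 + 0.932×0.068 = 0.0906
- alternative variance 2×0.96×0.04 = 0.0768
- n = (1.645√0.0906 + 1.282√0.0768)² / 0.04² ≈ 452 per arm
- 452 × 1.10 = 497.2, rounded up to 498

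The stated 498 is reproduced.

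**2. Effect on the standard error.** With two equal countries and balanced arms:

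- unstratified: SE = √(2·p̄(1−p̄)/498)
- stratified: SE = √(2·mean[p_k(1−p_k)]/498)

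The two variance terms differ by d²/4. At p̄ = 0.96, p̄(1−p̄) = 0.0384 and the unstratified SE is 1.242 points. At d = 8 points the stratified term is 0.0384 − 0.0016 = 0.0368, SE 1.216, and the ratio is √(0.0384/0.0368) = 1.0215.

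| Country cure, % | Stratified SE (points) | Unstratified SE too wide by | 90% half-width, unstratified → stratified (points) | True two-sided level of the plain 5% test | Power, unstratified → stratified |
|---|---|---|---|---|---|
| 96 / 96 | 1.242 | 0 | 2.043 → 2.043 | 0.0500 | 94.3% → 94.3% |
| 97 / 95 | 1.240 | 0.1% | 2.043 → 2.040 | 0.0497 | 94.3% → 94.3% |
| 98 / 94 | 1.235 | 0.5% | 2.043 → 2.032 | 0.0488 | 94.3% → 94.4% |
| 99 / 93 | 1.227 | 1.2% | 2.043 → 2.019 | 0.0473 | 94.5% → 94.7% |
| 100 / 92 | 1.216 | 2.2% | 2.043 → 2.000 | 0.0453 | 94.6% → 95.0% |

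Power is for the 4-point margin at one-sided 5%, with all 498 per arm analysed. Simulation of the plain test with no treatment effect gave rejection rates of 4.9% at 98/94 and 4.5% at 100/92, in agreement with the table.

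**3. If overall cure is lower than planned.** The share of the pooled variance that lies between countries is 1 − mean[p_k(1−p_k)] / [p̄(1−p̄)]. The power column is simulated with 224 evaluable per arm per country (249 less 10%).

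| Country cure, % | Mean, % | Between-country share | Power, unstratified → stratified |
|---|---|---|---|
| 96 / 90 | 93 | 1 − 0.06420/0.06510 = 1.4% | 76.2% → 76.6% |
| 96 / 85 | 90.5 | 1 − 0.08295/0.08598 = 3.5% | 66.0% → 67.0% |
| 90 / 75 | 82.5 | 1 − 0.13875/0.14438 = 3.9% | 47.4% → 48.7% |

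These means are below the design's 96%, and most of the lost power comes from the lower cure rate itself.

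**4. Country bias.** With 249 v 249 in both countries, the Mantel-Haenszel weights are equal. The stratified difference is then the average of the two country differences, which is also the pooled difference, so the bias is zero. If one arm has 259 and 239 patients by country and the other has 239 and 259, a gap of 4 points shifts the pooled difference by (20/498) × 4 = 0.16 points.

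**The case against.** The case for leaving this alone is fairly strong.

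- **Stratification is often left to the analysis plan.** True, and section 6.5 announces one. But section 6.4 already names the primary test, so the comment concerns a stated method.
- **Envelope batches are logistics and do not prove stratified randomisation.** This stands. A reader might infer that arms are fixed at 249 within each country as a design stratum. The protocol states a plan and gives no strata or blocks. Under simple unblocked randomisation the plain test has the right unconditional variance and is not too wide. Stratifying would then help by removing chance imbalance: with a 6-point gap, the 95% limit of the shift is about 1.96 × 6 × √(2×0.25/498) = 0.37 points.
- **A reader might infer that country imbalance biases the pooled comparison.** The planned split rules that out. A shift needs unequal realised numbers, dropout or per-protocol exclusions, and chance imbalance is not a systematic bias.
- **A reader might say that the protocol's confidence interval is too wide.** It names none, only p-values. The effect is on the test, or on any interval built from the same pooled variance.
- **Logistic regression could include country.** It could, since age and sex are only examples. But backward elimination might drop it, and an odds ratio cannot be set directly against a margin in percentage points.
- **No document shows that cure differs by country.** This stands. The size of the effect rests on assumption, and is zero if there is no gap.

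**Conclusion.** The point holds as a minor one. The primary test omits a factor around which recruitment is planned, and the consequence is mild conservatism. At 96% overall cure the standard error is 0 to 2.2% too wide and the power gain from stratifying is at most about 0.4 points, reached only at the extreme of 100% v 92%. In the lower-cure scenarios tried (means of 93% down to 82.5%) the gain is 0.4 to 1.3 points. All of this assumes a gap between countries that the protocol does not quantify, and the excess width also assumes that the planned balance is achieved. The test remains valid.

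A separate and weightier matter lies in the same sentence of section 6.4: a chi-square tests for a difference, whereas section 4 sets a one-sided equivalence objective. Stratifying the chi-square alone would not resolve that, and it adds no weight to the present point.

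**What to change.** In section 6.4 or the analytical plan:

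- Make the primary estimate the country-stratified (Mantel-Haenszel) risk difference in cure with its stratified confidence interval, at the one-sided 5% level of section 4, read against the 4-point margin.
- Apply it in both the intention-to-treat and per-protocol sets.
- Show the difference and its interval for each country.
- Stratify by country rather than centre so that the strata stay large (about 249 per arm as planned, 224 after 10% dropout).
- State in section 3.5 whether the randomisation list is stratified or blocked by country or centre, so that the analysis can be matched to it.

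The cost is wording only, settled before the analysis begins. It needs no extra patients and no new data.
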